# Effectiveness of personalized rehabilitation in adults suffering from persistent concussion symptoms as compared to usual care: a randomized control trial protocol

**DOI:** 10.1186/s12883-024-03700-5

**Published:** 2024-07-10

**Keywords:** Post-concussion syndrome, Concussion, Rehabilitation, Exercise, Headache

## Abstract

**Background:**

Symptoms reported by patients who sustain a concussion are non-specific. As such, clinicians are better able to manage patients when a standardized clinical exam is performed to sub-type the driver(s) of symptoms. Aerobic exercise and multimodal rehabilitation have consistently shown to be a possibly effective means to manage this population; however, the optimal training prescription is unclear. Thus, there is a need to further examine the effectiveness of personalized rehabilitative treatments. Our primary aim is to evaluate the response to personalized therapy on recovery, as measured by The Rivermead Post-concussion Symptoms Questionnaire (RPQ) when compared to an active control.

**Methods:**

We will conduct a multi-center 12-week case-crossover randomized controlled trial. 50 participants will be recruited from out-patient University Health Network clinics and community-based clinical practices around the greater Toronto area. Participants will be randomized at baseline to Group A: a personalized care program followed by an active control or Group B: an active control followed by a personalized care program. Participants will be included should they be 21 years of age and older and have symptoms that have persisted beyond 4 weeks but less than 1 year. Participants will undergo 6-weeks of care in their respective streams. After 6-weeks, participants will undergo a re-examination. They will then crossover and undertake the alternative treatment for 6 weeks. At the end of 12 weeks, participants will undertake the endpoint examinations. The primary outcome will be the Rivermead Postconcussion Questionnaire (RPQ). The secondary outcomes will be changes in standardized clinical examination, Neck Disability Index (NDI), Patient Health Questionnaire (PHQ-9) and an electroencephalography (EEG) via NeuroCatch^™^. The statistical analysis to be performed is composed of an adjusted model using an analysis of variance, specifically using an unpaired t-test to test for associations between variables and outcomes.

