## Background

Disabilities secondary to traumatic brain injury (TBI) are a major source of burden. Although the majority of patients who suffer a mild TBI (mTBI) recover, timelines are highly variable [1]. A recent large working group identified that up to 82% of patients report at least one symptom 6–12 months after a mTBI and that headaches appear to be the most common and pervasive symptom endorsed [2, 3]. Additionally, Graff et al. (2019) noted that mTBI has a long-term impact on labour markets. They found that 43% of patients don’t return to ordinary work 5-years post-injury [4]. The implications for this are significant for the person, the healthcare system and society. Thus, it’s imperative we further evaluate potentially beneficial treatments.

Unfortunately, there remains no agreed-upon biological basis for the symptom clusters reported by patients. The aggregate of symptoms reported by those suffering persistent symptoms is viewed as being non-specific. Leddy et al. (2015) showed that symptoms reported on a 22-item Post-concussion Symptom Scale questionnaire following a mild traumatic brain injury could not reliably discriminate between concussion subtypes [5]. Symptoms reported after a head injury traditionally have been ascribed to the brain, particularly cognitive symptoms. However, even cognitive complaints, including issues with concentration, brain fog and memory deficits have been reported after whiplash injuries [6]. This strongly suggests the need for clinicians managing this population to have performed a thorough examination.

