### Inclusion criteria

21-years and older.Meet the definition of postconcussion syndrome as defined by Tator et al. (2016), which requires a participant to report any 3 symptoms or more (from an inclusive list of the 40 most commonly reported persisting symptoms) lasting at least 1-month following the diagnosis of a concussion [13]. Concussion was defined according to the 6th International Consensus Statement on Concussion in Sport [10].Have adequate language skills in English to read and take part in rehabilitation treatment programs.Demonstrate an objective impairment on the baseline standardized exam, placing the participant into one of the three subgroups (autonomic, cervical or vestibulo-ocular).

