### Exclusion criteria

In-patients at Toronto Rehabilitation Institute or any other affiliated University Health Network clinics.Participants will be excluded should their clinical examination be unremarkable for any positive physical findings and therefore their dominant symptomatology places them into the Affective / Cognition subgroup described by Leddy et al. [7].Have a chronic infectious disease.Uncontrolled hypertension.Other neurological disorders (not attributed to their primary diagnosis).Cancer treatment (other than basal cell carcinoma), craniotomy, or refractory subdural hematoma.long-term use of psychoactive medications that would compromise their ability to comprehend and perform study activities.Those with pacemakers or elevated cardiovascular risk.Ongoing litigation surrounding their injury.Have been diagnosed with a moderate or severe brain injury prior to enrollment, or their post-concussive symptoms have persisted beyond 12 months.

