### Randomization and masking

We will use simple randomization to allocate participants to one of two sequences of interventions: Group A: personalized care program followed by active control; or Group B: active control followed by personalized care program. The study coordinator (NM) conducted the randomization using a randomized table generator (GraphPad Software Inc, La Jolla, CA). Randomization will be concealed; no other study personnel will be aware of the intervention assignments. However, it was not possible to blind the study coordinator (NM) as they are one of the main treating clinicians. Additionally, it was not possible to ensure adequate blinding of the participants, given the necessary thorough description of the treatment procedures that occurred during the informed consent process.

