### Statistical analysis

The primary outcome is a change in symptoms following rehabilitative interventions using the RPQ. Previous research examining the internal construct validity of the Rivermead Post-Concussion Symptom Questionnaire suggested that a score of 2 or more on at least 3 of the 16 symptoms represents an unfavourable outcome [40]. We chose to calculate the study sample size by assuming an effect size. Unfortunately, to date, no validated change scores exist, thus we prescribed a cut-off of 15% improvement as minimal clinically importance difference (MCID). This translates into a change of 2 points on the RPQ-3 and a change of 8 points on the RPQ-13. This agrees with prior clinical literature examining changes post-intervention on concussion symptoms [41]. Based on this effect size, a power of 80%, a significance level at *p* < 0.05 and a two-sided t-test, we calculated that a sample size of 50 participants was necessary [42].

Descriptive statistics will be applied to all outcome measures to assist in summarizing the results. Participant demographic data will be compared to assess compatibility between groups, specifically before the crossover point.

The statistical analysis conducted in this research is composed of an adjusted model using an analysis of variance to test for associations between variables and outcomes (two groups [personalized care or usual care] x 3 times [baseline, week 6 and 12]) [42]. The statistical analysis conducted in this study will be made using SAS OnDemand for Academics 2021. The data set is composed of six variables, two independent variables –personalized care group or usual care group – and four dependent variables – age, sex, and result of treatment on the RPQ graded as total score and sub-classification (RPQ-3 and RPQ-13). A 2-way analysis of covariance (ANCOVA) (two groups [personalized care or usual care] x 3 times [baseline, week 6 and 12] x baseline secondary outcomes [ERPs, NDI and PHQ-9] will be used to examine the effects of the rehabilitation programs while controlling for these covariates. Lastly, an unpaired t-test will be used to assess the effects of the rehabilitation programs on the secondary outcomes. In addition to the per-protocol analysis, an intention-to-treat analysis will be conducted.

All unintended effects, harms and/or dropouts during the program will be recorded.

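### Time since injury is not among the named covariates although entry spans about 1 to 12 months: a small loss of precision for the programme comparison, and a possible confounder in the search for markers of response

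*Protocol article*

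**What the plan says.** **Entry window.** The Abstract takes people who "have symptoms that have persisted beyond 4 weeks but less than 1 year". Under Inclusion criteria, symptoms must be "lasting at least 1-month following the diagnosis of a concussion". Under Exclusion criteria, people are left out if "their post-concussive symptoms have persisted beyond 12 months".

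**Natural course.** The Background says: "Although the majority of patients who suffer a mild TBI (mTBI) recover, timelines are highly variable". It gives no recovery rate by time since injury.

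**Allocation.** Randomization and masking states: "We will use simple randomization to allocate participants to one of two sequences of interventions". No stratification factor is named.

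**Model.** Statistical analysis lists "four dependent variables – age, sex, and result of treatment on the RPQ graded as total score and sub-classification (RPQ-3 and RPQ-13"). Age and sex are called dependent variables there; I read them as adjustment variables. An ANCOVA is added in which "baseline secondary outcomes [ERPs, NDI and PHQ-9] will be used to examine the effects of the rehabilitation programs while controlling for these covariates".

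**Balance check.** "Participant demographic data will be compared to assess compatibility between groups, specifically before the crossover point". Time since injury is not mentioned.

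**Marker aim.** Under Objectives, the tertiary aim relates baseline ERPs, neck disability and depression to whether a participant responds to treatment.

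**The concern.** A 6-week treatment period means something different at the two ends of the window. Someone entering at 5 weeks reaches 11 weeks, an increase of 6/5 = 120% in time since injury. For someone entering at 40 weeks the increase is 6/40 = 15%. If spontaneous improvement slows with time, the expected RPQ change over a period depends on when the participant enters. The protocol fixes its covariates by name and omits the variable that defines its own entry window.

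Two things are at stake. In the programme comparison, unexplained variation in spontaneous recovery widens the interval, and in a single trial of 50 it may fall unevenly between the sequences. In the marker analysis, time since injury could be related both to the marker and to the RPQ change, which is confounding in the ordinary sense.

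**Working it through.** **1. The plan's own figure.** Inputs from Statistical analysis: differences of 2 (RPQ-3) and 8 (RPQ-13) points, 80% power, two-sided 5%, t-test, N = 50. No SD is stated, so N cannot be reproduced directly. Taking 25 per sequence (no ratio is stated) and solving backwards gives a standardised difference of (1.96 + 0.84) × √(2/25) = 0.79, or 0.81 with the t distribution. An RPQ-13 SD of 10 (8/10 = 0.80) returns N = 50 by the normal formula and 52 by the t-test. SD 10 is used below as an assumption.

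**2. How uneven could entry times be by chance?**
- If time since injury is uniform over 1 to 12 months (assumption), its SD is 11/√12 = 3.2 months. The SE of the difference between sequences is 3.2 × √(2/25) = 0.90 month, a 95% range of about ±1.8 months.
- If 20%, 30% or 50% enter early (assumption), the early shares differ by 20 percentage points or more in 9%, 13% or 17% of simple randomisations.

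**3. Effect on the first-period comparison, two recovery rates.** All recovery inputs are assumptions: 30% early entrants; 3 RPQ-13 points per 6 weeks for late entrants; 6, 9 or 12 points for early entrants. The variance share is (early − late)² × 0.3 × 0.7 / 100. The shift from a 20-point imbalance is 0.2 × (early − late). Each scenario was simulated 40,000 times.

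| Early rate | Variance share | Shift at 20-point imbalance | Type I error, unadjusted / adjusted | Power at 8 points, unadjusted / adjusted | Equivalent N after adjustment |
|---|---|---|---|---|---|
| 6 (2-fold) | 1.9% | 0.6 | 5.1% / 5.1% | 78% / 78% | 50 |
| 9 (3-fold) | 7.6% | 1.2 | 5.0% / 5.1% | 78% / 80% | 46 |
| 12 (4-fold) | 17% | 1.8 | 5.2% / 5.2% | 78% / 84% | 42 |

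The shifts are 0.6/8 = 8% to 1.8/8 = 23% of the 8-point target.

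**4. The same check with a smooth curve.** Assume an RPQ-13 of 25 falling as a power of time since injury. The expected 6-week change is 25 × [1 − ((t+6)/t)^−b], with b from 0.2 to 0.5.
- At t = 5 weeks: 3.6 to 8.1 points. At t = 40 weeks: 0.7 to 1.7.
- SD of expected change over the window: 0.8 to 1.8. As a share of variance, 0.77²/100 = 0.6% to 1.8²/100 = 3.2%.
- Power with 25 per sequence: 79.1% unadjusted, 79.4 to 80.4% adjusted.
- 95% range of the chance difference from this source: 1.96 × SD × √(4/50) = ±0.4 to ±1.0 points. Total sampling error is 1.96 × 10 × √(4/50) = ±5.5.

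**5. What the crossover removes.** A within-person contrast with a period term cancels a trend common to both sequences. On the same curve, the change in weeks 0–6 and then 6–12 is 3.6 to 8.1 and then 1.8 to 3.3 for entry at 5 weeks, a slowing of 1.9 to 4.8. For entry at 40 weeks the slowing is 0.1 to 0.3. Half of a 20-point imbalance applied to the gap leaves 0.5 × 0.2 × (1.9 − 0.1) = 0.18 to 0.5 × 0.2 × (4.8 − 0.3) = 0.45 points. Little survives if that contrast is used.

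**6. The marker analysis.** Simulated with n = 50, a marker with no effect of its own, change SD 8, entry uniform over the window and the curve in step 4 (all assumptions). Regressing RPQ-13 change on the marker gives a false-positive rate of about 6 to 11% when the marker's correlation with time since injury is 0.5, and about 7 to 17% when it is 0.7. Adding log time since injury brings it back to about 5%.

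**The case against.** The case for leaving the plan alone is strong on the programme comparison. Randomisation makes any imbalance a chance event that the 5% error rate already covers, and step 3 confirms this. On the smooth curve the gain is about one power point at most, and the 6-point gain needs a 4-fold difference in recovery. Every participant receives both programmes, so a proper within-person analysis would remove most of what remains. The Background's remark on recovery concerns mild TBI in general, whereas this trial takes only people with symptoms already persisting and an objective impairment. All of this stands, with one limit. The group-by-time analysis of variance and the unpaired t-test state no within-person contrast or period term, so the crossover's protection is not assured.

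A reader might infer that recovery differs several-fold across the window and could pass for a programme effect. The document gives no such rate, and chance imbalance is not systematic bias. A reader might also infer that early entrants would reach 8 points untreated. That needs the steepest assumed curve and entry near week 5. On that curve with uniform entry about 2% of participants would do so, with exponents of 0.2 or 0.3 none would, and the trial has no untreated arm.

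On the marker aim, the objection is that no responder threshold or responder model is given, and that such detail may sit in a fuller plan. This limits how far the effect can be sized, but it does not restore the protection of randomisation, which that comparison lacks.

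**Conclusion.** The point holds as a minor improvement. The protocol names its adjustment variables and omits a plausible prognostic one that its eligibility rules already require to be dated.

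For the programme comparison, the consequence is a modest loss of precision and some exposure of the single realised result to chance imbalance: 0 to 6 power points, and a first-period shift of 0.6 to 1.8 RPQ-13 points at a 20-point imbalance. It is not bias. For the marker aim, an unadjusted analysis could credit a marker with an effect that belongs to natural recovery. The illustrative false-positive rates of 6 to 17% depend on an assumed correlation of 0.5 to 0.7. All sizes rest on assumed recovery rates, entry distributions and SDs, since the document supplies none. If recovery differs little across the window, the gain is negligible.

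**What to change.** - In Statistical analysis, add log time since injury at randomisation as a prespecified covariate in the RPQ model, in addition to those already named. The document gives no basis for ranking the existing covariates, so none should be exchanged for it.
- State the date from which time is counted, since the criteria refer both to diagnosis and to symptom duration.
- Include the same term in the analyses serving the tertiary aim, and call a marker predictive only after allowing for it.
- Show time since injury by sequence in the baseline comparison.

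The cost is a few lines of wording and one degree of freedom per model. No new data are needed, because the 12-month limit cannot be applied without dating the injury or the onset of symptoms. The randomisation and the clinical procedures are unchanged.

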**Discussion:**

Given the recommendations from reviews on the topic of rehabilitation for adults with persistent concussion symptoms, we are undertaking a controlled trial. The documented high costs for patients seeking care for persistent symptoms necessitate the need to evaluate the effectiveness of a personalized rehabilitative program compared to the current standard of care.

**Trial registration:**

ClinicalTrials.gov ID: NCT06069700.

**Supplementary Information:**

The online version contains supplementary material available at 10.1186/s12883-024-03700-5.

## Background

Disabilities secondary to traumatic brain injury (TBI) are a major source of burden. Although the majority of patients who suffer a mild TBI (mTBI) recover, timelines are highly variable [1]. A recent large working group identified that up to 82% of patients report at least one symptom 6–12 months after a mTBI and that headaches appear to be the most common and pervasive symptom endorsed [2, 3]. Additionally, Graff et al. (2019) noted that mTBI has a long-term impact on labour markets. They found that 43% of patients don’t return to ordinary work 5-years post-injury [4]. The implications for this are significant for the person, the healthcare system and society. Thus, it’s imperative we further evaluate potentially beneficial treatments.

Unfortunately, there remains no agreed-upon biological basis for the symptom clusters reported by patients. The aggregate of symptoms reported by those suffering persistent symptoms is viewed as being non-specific. Leddy et al. (2015) showed that symptoms reported on a 22-item Post-concussion Symptom Scale questionnaire following a mild traumatic brain injury could not reliably discriminate between concussion subtypes [5]. Symptoms reported after a head injury traditionally have been ascribed to the brain, particularly cognitive symptoms. However, even cognitive complaints, including issues with concentration, brain fog and memory deficits have been reported after whiplash injuries [6]. This strongly suggests the need for clinicians managing this population to have performed a thorough examination.

Leddy et al. (2021) proposed a systematic clinical examination to help identify one or more clinical profiles of the post-concussion patient [7]. The identified clinical profile(s) would theoretically assist the treatment provider(s) in providing targeted therapies to optimize recovery. Leddy et al. (2021) noted that specifically including graded physical exertion testing will assist with identifying patients who exhibit cardinal features of an autonomic dysfunction concussion profile when they demonstrate exercise intolerance. Exercise intolerance is defined as an inability to exercise at an age-appropriate threshold due to the exacerbation of concussion symptoms [7]. When patients can exert themselves and achieve near their age-appropriate maximum heart rate without exacerbation of symptoms, then the etiology or justification for persisting concussion symptoms is thought to be due to an alternative problem such as a cervical spine disorder, vestibular-ocular impairment, or mood/cognition related issues [7].

Numerous pharmacological and non-pharmacological treatments have been utilized and studied in an attempt to treat persistent concussion symptoms. Specifically, symptom-limited aerobic exercise appears to be a staple therapy included in most trials assessing improvements in persistent symptoms [8, 9]. Further, the most recent consensus statement on concussion in sport from the 6th International Conference on Concussion in Sport recommends patients be treated for persisting symptoms via symptom-limited aerobic exercise [10]. Rytter et al. (2021) noted that following a systematic review and meta-analysis of 19 randomized clinical trials, there is weak evidence for nonpharmacological interventions, including advice, use of graded physical exercise, manual therapy to the neck, vestibular therapy and interdisciplinary rehabilitation [11]. Continuing, Moser et al. (2023) reported that multimodal rehabilitative therapy consistently demonstrates the strongest level of evidence among the various nonpharmacological treatments studied to date for physically dominant persistent symptoms [12]. Multimodal therapy was defined as the use of multiple treatment modalities concurrently for patients provided by either an interdisciplinary team or a single practitioner [12]. Similarly to the conclusions of Rytter et al., the authors note that the majority of trials suffer methodological weakness such as consistently failing to include a treatment control group, not recruiting sufficient participants to properly power the trial, or failing to use reliable and validated clinical outcome measures [12]. Given the preliminary findings for exercise and multimodal therapy, they suggest further research in this area.

### Objectives

The present study was developed to better understand the effects of personalizing rehabilitative treatments for patients with persistent concussion symptoms. Our primary aim is to evaluate the effectiveness of a personalized rehabilitation program based on subgroup classification, as measured by The Rivermead Post-concussion Symptoms Questionnaire (RPQ) when compared to an active control. Specifically, the objective is to assess whether personalizing rehabilitation following a standardized examination affords improved recovery when compared to an active control, which is reflective of the current standard of care for this population. Given symptoms are non-specific, we hypothesize that participants undergoing a personalized rehabilitation program derived from subgroup classification following a standardized exam will demonstrate clinically meaningful and statistically significant improved Rivermead Postconcussion Questionnaire scores when compared to the active control whose therapy approach is based on general rehabilitation recommendations.

Our secondary aim is to examine participants’ cognition Pre and Post-treatment (6 and 12-week follow-up points) via a quantitative electroencephalogram (EEG). Due to the various ostensible drivers of impaired cognition in this population, such as neck pain, sleep impairment, and altered mood, the EEG will serve as an objective cognitive evaluation.

Our tertiary aim is to examine at baseline and the follow-up points, participants’ Neck Disability Index, Patient Health Questionnaire (PHQ-9) and electrophysiological brain activity changes as measured by quantitative EEG. These outcomes will be compared to the standardized clinical examination findings as well as the RPQ. This will be done to identify any possible neuro-biomarker (abnormal ERPs), level of perceived neck disability or baseline level of depression that is predictive of treatment responders versus non-responders.

